# Testing non-inferiority of blended versus face-to-face cognitive behavioural therapy for severe fatigue in patients with multiple sclerosis and the effectiveness of blended booster sessions aimed at improving long-term outcome following both therapies: study protocol for two observer-blinded randomized clinical trials

**DOI:** 10.1186/s13063-019-3825-2

**Published:** 2020-01-20

**Keywords:** Multiple sclerosis, Fatigue, Cognitive behavioural therapy, Long-term effectiveness, Booster sessions, Blended care, Internet, Study protocol, Randomised clinical trial, Non-inferiority trial

## Abstract

**Background:**

Cognitive behavioural therapy (CBT) has been found to be effective in reducing fatigue severity in MS patients directly following treatment. However, long-term effects are inconsistent leaving room for improvement. In addition, individual face-to-face CBT draws heavily on limited treatment capacity, and the travel distance to the treatment centre can be burdensome for patients. Therefore, we developed “MS Fit”, a blended CBT for MS-related fatigue, based on a face-to-face CBT protocol found effective in a previous study, and “MS Stay Fit”, internet-based booster sessions to improve long-term effectiveness of CBT for MS-related fatigue. This article presents the protocol of two randomised clinical trials (RCTs) conducted within one study investigating (1) the non-inferiority of MS Fit compared with evidence-based face-to-face CBT for MS-related fatigue and (2) the effectiveness of MS Stay Fit on the long-term outcome of fatigue compared with no booster sessions.

**Methods/design:**

The first part of this study is an observer-blinded non-inferiority multicentre RCT, in which 166 severely fatigued MS patients will be randomly assigned (1:1 ratio, computer-generated sequence) to either face-to-face CBT or blended CBT (MS Fit) for fatigue. The primary endpoint is at 20 weeks after baseline. After this post-treatment assessment, patients will be randomly assigned again (1:1 ratio, computer generated sequence) to either MS Stay Fit consisting of two booster sessions at 2 and 4 months after end of treatment or no booster sessions. The primary endpoint of the second study is 52 weeks after baseline. Primary outcome measure in both studies is fatigue severity assessed with the fatigue severity subscale of the Checklist Individual Strength (CIS20r). Outcomes will be assessed at baseline (T0), at the end of treatment (T20), and after 39 and 52 weeks (T39 and T52).

**Discussion:**

If MS Fit is found to be non-inferior to face-to-face CBT, it will improve the accessibility of this treatment. In addition, the study aims to test whether it is possible to improve long-term effectiveness of CBT for MS-related fatigue with MS Stay Fit.

**Trial registration:**

Dutch Trial Register (NTR6966), registered 18 January 2018 https://www.trialregister.nl/trial/6782

**World Health Organization (WHO) Trial Registration Data Set:**

All items from the WHO Trial Registration Data Set can be found within the protocol.

## Background

Multiple sclerosis (MS) is a neurodegenerative disease characterized by demyelination, axonal loss and inflammation of the central nervous system that usually appears between the age of 20 and 40. MS can cause a variety of symptoms such as motor weakness, sensory deficits, impaired balance, fatigue, depression and pain. Fatigue is one of the most often reported symptoms in MS (75–90%) [1–4], and half of the patients with MS even report it to be one of the most burdensome symptoms affecting their daily functioning and worsening other MS symptoms [5].

The aetiology of MS-related fatigue is not clear and is likely to be multifactorial. In a cognitive-behavioural model, van Kessel and Moss-Morris proposed that where disease-related factors, such as inflammation and neurodegeneration, may initially cause fatigue, psychological mechanisms play an important role in perpetuating and increasing fatigue [6]. These mechanisms consist of cognitive, emotional and behavioural responses to fatigue (for example, catastrophizing cognitions, depression, helplessness, all-or-nothing behaviour, avoidance, and sleep problems). Based on this model, a cognitive behavioural therapy (CBT) was developed, aimed at decreasing fatigue, in which patients learn to change unhelpful beliefs and behaviours regarding fatigue [7, 8].

Although in clinical practice treatments for MS-related fatigue often include energy conservation management, exercise therapy, and multidisciplinary interventions, recent systematic reviews and meta-analyses of randomised clinical trials (RCTs) have shown CBT to be an effective treatment for reducing fatigue. There is no evidence for effectiveness of pharmaceuticals or multidisciplinary rehabilitation treatment [9–12]. In the recent TREFAMS-ACE programme, TREFAMS being an acronym for TReating FAtigue in Multiple Sclerosis, three RCTs were conducted studying the effectiveness of respectively Aerobic Exercise Training (TREFAMS-AT), Cognitive Behavioural Therapy (TREFAMS-CBT) and individual Energy Conservation Management (TREFAMS-ECM), compared with MS nurse consultations on fatigue [13]. Results showed that aerobic exercise training and energy conservation management did not lead to a significant or clinically relevant reduction of fatigue [14, 15], whereas the TREFAMS-CBT trial showed that MS-related fatigue can be reduced significantly with individual face-to-face CBT carried out by trained psychologists [16], although 1-year follow-up measurements showed that the effect of CBT had worn off over time. More studies have shown that fatigue in MS can be treated effectively with CBT [8, 17–19]. However, CBT was applied in different forms and protocols (individual and group formats, internet-based or face-to-face), and long-term effects differed between studies [20]. Analysis of cognitive-behavioural variables mediating the fatigue relapse in the TREFAMS-CBT study showed that increased daytime sleepiness, more problems in staying physically active and an increase of subjective cognitive problems (i.e., concentration) mediated the fatigue relapse after 1 year [7]. However, in these analyses, only a limited number of possible mediating factors were included. More research is needed to determine which other factors are responsible for the increase in fatigue at long-term follow-up.

Face-to-face CBT draws heavily on limited treatment capacity and requires patients to travel and schedule appointments which is burdensome for fatigued patients. Therefore, blended CBT, in which online treatment is combined with limited face-to-face contacts or video consultations with the CBT therapist, might be an attractive treatment option for severely fatigued patients with MS. Several studies have been conducted on the effectiveness of internet-based CBT for MS-related fatigue, showing positive results [17, 18, 21]. However, it remains unclear whether the effectiveness of blended CBT is comparable to that of face-to-face CBT in treating primary MS-related fatigue.

In the proposed study, two RCTs will be conducted to answer the following two research questions:
Is blended CBT (MS Fit) non-inferior with respect to its effect on fatigue severity compared with evidence-based face-to-face CBT in severely fatigued patients with MS?Do blended CBT booster sessions (MS Stay Fit) improve long-term outcome with respect to fatigue severity at 1-year follow-up compared with no booster sessions?

To this purpose, “MS Fit”, an internet-based version of the CBT intervention used in the TREFAMS study, was developed [16]. In the MS Fit study group, patients will receive two face-to-face sessions with a CBT therapist and will be supported during their online treatment by video consultations and email contact. The online sessions of MS Fit are also based on the online CBT previously found to be effective in treating severe fatigue in patients with type 1 diabetes mellitus [22], breast cancer survivors [23] and patients with chronic fatigue syndrome [24].

In addition, “MS Stay Fit”, a blended booster programme consisting of several optional online booster modules and two video consultations with the therapist 2 and 4 months after finishing the initial CBT, has been developed. To our knowledge, this will be the first study testing the effectiveness of booster sessions in sustaining the effects of CBT for chronic fatigue. In this article, the SPIRIT (Standard Protocol Items: Recommendations for Interventional Trials) reporting guideline is used [25].

## Method/design

The first part of the study is an observer-blinded non-inferiority multicentre RCT, in which patients who are eligible to participate will be randomly allocated to either the face-to-face CBT intervention or MS Fit [26, 27]. Both groups will receive CBT for 20 weeks, and after a post-treatment assessment, patients who complete the second assessment will be randomly assigned again to MS Stay Fit or receiving no booster sessions. Patients who drop out of the initial treatment or study will not be randomly assigned for the second RCT. All patients will be assessed at baseline (T0), post-treatment (T20), after 9 months (T39) and after 1 year (T52) (Fig.1). See Additional file 1: Table S1 for all items of the World Health Organization (WHO) Trial Registration Data Set.

**Fig. 1 Fig1:**
[figure not shown]
Study design

### Participants

The 166 patients required for the non-inferiority RCT will have to meet the same inclusion criteria as in the TREFAMS-CBT study [13, 26, 27]: (a) definitive diagnosis of MS, (b) severely fatigued, (c) age of between 18 and 70, (d) ambulatory, (e) no evident signs of an exacerbation and no corticosteroid treatment in the past 3 months, (f) no current infections, (g) no anaemia, and (h) a normal thyroid function. The exclusion criteria are (a) depression, (b) primary sleep disorders, (c) other severe somatic or psychiatric co-morbidity, (d) current pregnancy or having given birth in the past 3 months, (e) pharmacological treatment for fatigue that was started in the past 3 months, (f) non-pharmacological therapies for fatigue that took place in the last 3 months, (g) having received CBT in the TREFAMS trial. This last exclusion criterion is added for this study. See Table 1 for the operationalization of the inclusion and exclusion criteria. As effectiveness of the booster programme can be measured only if patients have completed the initial treatment, the following additional inclusion criteria were defined for participation in the second randomized clinical trial testing the effectiveness of MS Stay Fit: (a) having started treatment (i.e., formulated treatment goals after the first session of CBT or MS Fit); (b) having finished the initial treatment period with a face-to-face session and assessment at T20.

**Table 1 Tab1:** Inclusion and exclusion criteria of the non-inferiority trial

Inclusion criteria	Exclusion criteria
a. Definitive diagnosis of MS confirmed by a neurologist	a. Depression (BDI >4 and meeting criteria of depression as assessed by MINI)
b. Severely fatigued (CIS20r fatigue ≥35)	b. Primary sleep disorders (anamnesis)
c. Age between 18 and 70	c. Severe co-morbidity (CIRS item ≥3)
d. Ambulatory patients (EDSS ≤6)	d. Current pregnancy or having given birth in the past 3 months
e. No evident signs of an exacerbation, or corticosteroid treatment in the past three months	e. Pharmacological treatment for fatigue that was started in the past 3 months
f. No current infections (anamnesis)	f. Non-pharmacological therapies for fatigue that took place in the last 3 months
g. No anaemia (anamnesis)	g. Receiving CBT in the TREFAMS-CBT trial
h. A normal thyroid function (anamnesis)	

*Abbreviations*: *BDI* Beck Depression Inventory, *CBT* cognitive behavioural therapy, *CIRS* Cumulative Illness Rating Scale, *CIS20r* Checklist Individual Strength, *EDSS* Expanded Disability Status Scale, *MINI* mini international neuropsychiatric interview, *MS* multiple sclerosis, *TREFAMS* TREating FAtigue in MS

### Sample size calculation

#### Non-inferiority trial (RCT 1)

If there is truly no difference between the face-to-face CBT and blended CBT, then 150 patients are required to be 80% sure that the lower limit of a one-sided 95% confidence interval (CI) will be above the non-inferiority margin of −5.3 points on the Checklist Individual Strength (CIS20r) fatigue severity subscale. Adjusting for a dropout of 10%, 166 participants need to be included (two groups of 83) [26–28]. The non-inferiority margin was defined on the basis of statistical reasoning (i.e., by using the TREFAMS-CBT results) and clinical judgement [16]. In the TREFAMS-CBT trial, the difference in the change score between CBT and MS nurse consultations for fatigue was 6.67 points (95% CI 2.70–10.68) on the CIS20r fatigue severity subscale [16]. In accordance with the recommendations of the US Food and Drug Administration [26], the following formula was used to derive the margin of non-inferiority: the mean effect 6.67 - 50% of the lower limit of the 95% CI of the TREFAMS-CBT effect at week 16 (i.e. 2.7), that is, 6.67–1.35 = 5.32. A 1.35 point loss in effectiveness of blended CBT compared with TREFAMS-CBT is considered as clinically acceptable [16]. Tummers et al. [28] derived the same non-inferiority margin of 5.3 points on the CIS20r fatigue severity subscale through post-hoc analysis of the course in the waiting list of an RCT testing the efficacy of CBT in patients with chronic fatigue syndrome. The margin of 5.3 points reflects the largest loss of effect in the blended CBT group that would be clinically acceptable.

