#### Booster trial (RCT 2)

This RCT concerns a superiority between-group comparison at 1-year follow-up of MS Stay Fit (i.e., web-based booster sessions combined with email contact and video consultations versus no booster sessions). Treatment effects on fatigue are assumed to be maintained with additional booster sessions but to gradually wear off to the fatigue level at baseline in the study group without additional booster therapy sessions. In the TREFAMS-CBT study, the treatment effects gradually wore off directly post-treatment until 1 year after the start of treatment [16]. At 1-year follow-up, fatigue levels in the CBT group were comparable to the level of fatigue at baseline. A between-group difference of 6.7 points on CIS20r fatigue is expected. Two-sided significance testing with an α of 5%, two study groups of 75 participants at 1 year, will result in a power of 98%. Therefore, the total number of enrolled patients (two groups of 83, i.e., 75 patients plus a 10% attrition rate) yields sufficient power in RCT 2 to address the second research question.

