**Fig. 3 Fig3:**
[figure not shown]
Illustration of a possible result of the non-inferiority tria. Difference between face-to-face CBT and blended CBT and the 95% CI. H0: blended CBT is inferior to face-to-face CBT, meaning that face-to-face CBT – blended CBT ≥ M. Mis the non-inferiority margin (6.67–5.32 = 1.35). H1: blended CBT is non-inferior to face-to-face CBT, meaning that face-to-face CBT – blended CBT < Ml

To compare the effect of blended care and face-to-face CBT on the secondary outcome measures, the ITT mixed model analysis will be repeated with the secondary outcomes at the end of treatment (T20) as dependent variable and study group as fixed factor.

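### The stated powers of RCT 1 (80%) and RCT 2 (98%) do not agree under any single standard deviation, and RCT 2's 75 per arm at week 52 leaves no room for loss after week 20

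*Protocol article*

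**What the plan says.** All of this is in the protocol article.

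- **RCT 1** (Sample size calculation, Non-inferiority trial): the starting assumption is "If there is truly no difference between the face-to-face CBT and blended CBT". On that basis "150 patients are required to be 80% sure that the lower limit of a one-sided 95% confidence interval (CI") clears the margin. The margin is explained thus: "The margin of 5.3 points reflects the largest loss of effect in the blended CBT group that would be clinically acceptable". A 10% dropout allowance takes 150 to 166.
- **RCT 2** (Sample size calculation, Booster trial): a 6.7-point difference is expected, tested two-sided at 5%, and "two study groups of 75 participants at 1 year, will result in a power of 98" per cent. The enrolled total is described as "two groups of 83, i.e., 75 patients plus a 10% attrition rate".
- **Entry to RCT 2** (Method/design): "Patients who drop out of the initial treatment or study will not be randomly assigned for the second RCT". The Participants section adds that patients must have started treatment, finished the initial treatment period and been assessed at T20.
- **Outcome** (Primary outcome measure): the same subscale in both trials, at T20 for RCT 1 and T52 for RCT 2.
- **Fig. 3 caption**: "Difference between face-to-face CBT and blended CBT and the 95% CI", with no side named.

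Neither calculation gives an SD, a baseline correlation or a variance adjustment.

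**The concern.** The two calculations share the outcome scale and the number per arm, so each stated power fixes the SD behind it. If those SDs differ and nothing explains why, a reader cannot tell which power to believe. Either RCT 2 is less well powered than claimed, or RCT 1 is considerably larger than its stated 80% requires.

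The attrition allowance raises a second question. RCT 2 draws only on patients still in the study at T20, so an allowance already spent by T20 cannot also cover losses between T20 and T52.

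**Working it through.** **Inputs.** RCT 1: n = 75 per arm, margin 5.3, true difference 0, one-sided α = 0.05, power 80%. RCT 2: n = 75 per arm, difference 6.7, two-sided α = 0.05, power 98%. Enrolment 166, attrition 10%. Further loss after T20: 10%, my assumption, since the article gives no figure.

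**The plan's own figures.** Enrolment reproduces within rounding: 150/0.9 = 166.7 and 150 × 1.1 = 165, against 166. The two powers cannot be reproduced directly without an SD, so I solve for it by normal approximation.

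**Implied SDs.** SD = difference / (z for α + z for power) × √(n/2), with √(75/2) = 6.124.

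- RCT 1: 5.3 / (1.645 + 0.842) × 6.124 = **13.05** (12.99 with the noncentral t).
- RCT 2: 6.7 / (1.960 + 2.054) × 6.124 = **10.22** (10.16 with the noncentral t).

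The ratio of variances is (13.05/10.22)² = 1.63.

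**Could rounding or another reading close the gap?**

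- Letting the 98% stand for anything from 97.5% to 98.5% gives SD 10.47 to 9.93.
- Using 83 rather than 75 per arm in RCT 2 gives SD 10.75.
- Reading RCT 1 at one-sided 2.5% gives SD 11.58, at which RCT 2 has 94.3% power.

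None of these yields one SD for both trials.

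**Each SD carried into the other trial.**

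- RCT 2 at SD 13.05: standard error 13.05 × √(2/75) = 2.131; 6.7/2.131 − 1.960 = 1.184; power **88%**.
- RCT 1 at SD 10.22: standard error 1.669; 5.3/1.669 − 1.645 = 1.531; power **94%**.
- Size for 80% in RCT 1 at SD 10.22: 2 × (1.645 + 0.842)² × 10.22² / 5.3² = 46 per arm, **92 in total**.

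**Sample flow.** 166 × 0.9 = 149.4 at T20, about 75 per arm. That is already the number claimed for T52, so it allows no loss over the next 52 − 20 = 32 weeks. With the assumed second 10%, 149.4 × 0.9 = 134.5, about 67 per arm.

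**RCT 2 power with 67 per arm.**

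- SD 10.22: 6.7 / (10.22 × √(2/67)) − 1.960 = 1.83; power **97%**.
- SD 13.05: 6.7 / (13.05 × √(2/67)) − 1.960 = 1.01; power **84%**.

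**Side of the interval.** If the Fig. 3 interval were two-sided 95% (one-sided 2.5%), RCT 1 with 75 per arm would have:

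- SD 13.05: 5.3/2.131 − 1.960 = 0.527; power 70%.
- SD 10.22: 5.3/1.669 − 1.960 = 1.216; power 89% (90% at SD 10).

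**The case against.** **The SDs may really differ.** No SD is printed, so nothing printed is contradicted outright. The endpoints are 32 weeks apart, RCT 2 takes only patients who finished treatment, and its no-booster arm is assumed to drift back to baseline fatigue, where entry required a score of 35 or more. For illustration, an SD of 13 with boosters and 6.3 without (an even spread over 35 to 56) pools to √((169 + 39.7)/2) = 10.2, which gives 98% power. Adjustment for a covariate correlated about 0.62 with the outcome, in RCT 2 alone, would also take 13.05 to 10.22. This much stands: a reader might infer that at least one power must be wrong, and the document does not prove that. But both explanations are supplied from outside. The first is generous, because week-52 scores are not cut off at 35. As for the second, the Statistical analyses section describes the same kind of mixed model for both trials and names only group as a fixed factor.

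**An article may leave the SD to the full protocol.** True, and its absence alone would be no finding. The point is that the figures the article does print agree only if an unstated assumption is added.

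**Fig. 3.** A reader might infer that text and figure use different confidence levels. They do not: both say 95%, and the caption names no side. The sample size section is the only explicit statement, and it says one-sided. The caption is an ambiguity to remove, not a rival rule.

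**A tempting reconstruction.** SD 10, 90% power and one-sided 2.5% give 2 × (1.960 + 1.282)² × 100 / 5.3² = 74.8 per arm in RCT 1 and 98.4% power in RCT 2. A reader might infer that these were the real inputs. That is conjecture: 75 per arm follows equally well from the stated 80% and one-sided 5% with SD 13.05.

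**Attrition.** If fewer than 10% are lost by T20, some room remains for later loss. The Participant retention and Participant withdrawal sections also ask for at least the CIS20r fatigue score from people who decline the full set or leave. Both soften the effect, and power stays above 80% in every case computed for RCT 2. The stated T52 size still does not follow from the stated allowance.

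**Conclusion.** The concern holds in a limited form. Under any one SD, the 80% for RCT 1 and the 98% for RCT 2 cannot both be right with 75 per arm, and the article gives no reason for two SDs or for a variance adjustment in RCT 2 alone. The discrepancy is about 10 percentage points of power in RCT 2 (88% against 98%) or about 14 in RCT 1 (94% against 80%), depending on which SD is true.

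The 75 per arm at T52 uses an allowance already spent at T20. Under an assumed further 10% loss, that matters little at SD 10.22 (97%) and more at SD 13.05 (84%). The article's conclusion that RCT 2 has sufficient power survives in either case; its 98% may not.

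These results rest on the normal approximation, equal arms, equal variances within each trial and no covariate adjustment. They do not show which SD was used, and they give no ground for moving the primary interval to two-sided 95%. That would change an explicit decision rule while recruitment is under way and could leave RCT 1 at about 70% power.

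**What to change.** 1. Retrieve the original calculation. State for each trial the SD, its source and any covariate adjustment. If the SDs differ, say why; if not, restate whichever power is wrong.
2. Give attrition before T20 and between T20 and T52 as separate figures, and restate RCT 2's week-52 size and power from them.
3. Make the Fig. 3 caption name the same one-sided 95% interval as the sample size section. If a two-sided interval was always intended, say so in both places and restate RCT 1's power for it (about 70% at SD 13.05, about 90% at SD 10).

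The cost is a check of existing records and some corrected figures. Enrolment does not change, and under the one-sided reading neither does the analysis. If the larger SD proves right, the published power of RCT 2 will look less favourable.

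### RCT 1 carries two incompatible non-inferiority margins, 5.3 and 1.35 points, and the larger one exceeds the lower confidence limit of the historical CBT effect (2.70)

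*Protocol article*

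**What the plan says.** All statements are in the protocol article. Margins are given here as a loss in points on the CIS20r fatigue severity subscale, that is, the face-to-face effect minus the blended effect.

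**Sample size calculation, Non-inferiority trial (RCT 1):**
- The historical difference in change score between CBT and MS nurse consultations "was 6.67 points (95% CI 2.70–10.68) on the CIS20r fatigue severity subscale".
- The margin is "the mean effect 6.67 - 50% of the lower limit of the 95% CI of the TREFAMS-CBT effect at week 16", worked out as "6.67–1.35 = 5.32".
- The next sentence reads: "A 1.35 point loss in effectiveness of blended CBT compared with TREFAMS-CBT is considered as clinically acceptable".
- A trial in chronic fatigue syndrome is then cited as having reached the same 5.3 from the course in its waiting list.
- The paragraph closes: "The margin of 5.3 points reflects the largest loss of effect in the blended CBT group that would be clinically acceptable".
- The sizing statement is that "150 patients are required to be 80% sure" that the lower limit of a one-sided 95% confidence interval "will be above the non-inferiority margin of −5.3 points".

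**Statistical analyses, Non-inferiority of blended CBT compared with face-to-face CBT at 20 weeks:** the result is to be shown on a graph with the margin, as in Fig. 3. The Fig. 3 legend writes H0 and H1 in terms of M and defines M as 6.67 minus 5.32, which is 1.35.

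**The concern.** A non-inferiority trial has one decision threshold, and this protocol prints two. The sample size rests on 5.3; the written hypotheses rest on 1.35; the paragraph that derives the margin calls each of them the acceptable loss. If both stand when the data are analysed, the primary conclusion depends on which section is followed, and a choice made after the result is known would not be credible.

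The two numbers are complements: 1.35 + 5.32 = 6.67. By the article's own sentence, 1.35 is what may be lost, so 5.32 is what should be kept. The formula then uses the part to be kept as the permitted loss.

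The size of the margin also matters for the claim. The Discussion intends a non-inferior result to support implementation of blended CBT. That needs some assurance that benefit over the historical comparator survives, and a margin above 2.70 does not give it by itself.

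**Working it through.** **Inputs from the article:** effect 6.67, 95% CI 2.70 to 10.68; margins 5.3 and 1.35; one-sided 5%; 80% power at a true difference of 0; 75 evaluable per arm. For RCT 2: difference 6.7, two-sided 5%, 75 per arm, power 98%.

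**1. The plan's figure.** 0.5 × 2.70 = 1.35 and 6.67 − 1.35 = 5.32. The arithmetic reproduces. The legend's 6.67 − 5.32 = 1.35 is the same sum reversed.

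**2. Size of 5.32.**
- 5.32 / 2.70 = 1.97, or 197% of the lower limit.
- 5.32 / 6.67 = 0.80; the remainder, 1.35 / 6.67, is 20% of the point estimate.
- If the true effect is 2.70, a loss of 5.32 leaves 2.70 − 5.32 = −2.62, worse than nurse consultation. If it is 6.67, the loss leaves +1.35.

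**3. Standard deviation (assumption).** None is stated, so it is back-solved.
- RCT 1: SD = 5.3 / (1.645 + 0.842) × √(75/2) = 13.05.
- RCT 2: SD = 6.7 / (1.960 + 2.054) × √(75/2) = 10.22.

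With SE = SD × √(2/75), these give SE = 2.13 and 1.67.

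**4. How often the two margins disagree.** The chance of meeting margin m at true loss d is Φ((m − d)/SE − 1.645). At d = 0:

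| SD | m = 5.3 | m = 2.70 | m = 1.35 |
|---|---|---|---|
| 13.05 | 80% | 35% | 15.6% |
| 10.22 | 93.7% | 49% | 20.2% |

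The trial passes 5.3 but fails 1.35 with probability 80.0 − 15.6 = 64.4% (SD 13.05) or 93.7 − 20.2 = 73.5% (SD 10.22). An observed difference of exactly zero gives a limit of 1.645 × 2.13 = 3.5 or 1.645 × 1.67 = 2.7, both between the two margins.

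**5. A blended therapy equal to nurse consultation, judged at 5.3.** The true loss then equals the true face-to-face effect.

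| True face-to-face effect | SD 13.05 | SD 10.22 |
|---|---|---|
| 2.70 | Φ(2.60/2.13 − 1.645) = 34% | Φ(2.60/1.67 − 1.645) = 47% |
| 6.67 | Φ(−1.37/2.13 − 1.645) = 1.1% | Φ(−1.37/1.67 − 1.645) = 0.7% |

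**6. Patients needed for smaller margins** (one-sided 5%, 80% power, true difference 0). For 1.35: 1,156 per arm (SD 13.05) or 709 (SD 10.22). For 2.70: 289 or 178 per arm.

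**The case against.** Four points can be made for the plan.

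- **The 1.35 sentence may be a slip.** The authors may have meant 1.35 as the part of the effect that must remain, with 5.32 as the permitted loss. That is possible, but the text says loss, and the Fig. 3 legend independently makes 1.35 the margin in H0 and H1. Whichever was meant, at least one section has to change.
- **5.3 has other support.** The article also cites clinical judgement and the chronic fatigue syndrome derivation. This stands: 5.3 cannot be called baseless. The second source concerns another population and a waiting list, however, so it does not tie the permitted loss to the CBT effect in MS.
- **The consequence is conditional.** A reader might infer that the plan would readily pass a blended therapy no better than nurse consultation. The documents do not support that as a general statement. The 34% to 47% holds only if the true face-to-face effect sits at the lower confidence limit; at the point estimate the chance is about 1%. Under the hypotheses as written in the Fig. 3 legend, a loss of 2.70 would count as inferior.
- **The regulatory attribution cannot be judged here.** A reader might also infer that the formula misstates the cited guidance. That source is not at hand, so the attribution should be verified and not presumed wrong. The internal contradiction does not depend on it.

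**Conclusion.** The point holds as an unreconciled decision threshold. The article sizes RCT 1 on 5.3, writes its hypotheses on 1.35, and calls both the acceptable loss. If the therapies are truly equal, the two give opposite conclusions with probability 64% to 74%. By the article's own sentence on the 1.35-point loss, the formula uses the complement of the intended quantity.

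Separately, 5.3 is 197% of the historical lower limit and 80% of the point estimate, so meeting it shows only that blended CBT is not more than 5.3 points worse. It neither shows nor rules out benefit over nurse consultation; that depends on where the true face-to-face effect lies between 2.70 and 6.67 or beyond.

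The contradiction itself needs no assumption. The probabilities rest on normal theory, 75 per arm, and SDs of 13.05 and 10.22, back-solved from RCT 1 and RCT 2 respectively. This must be corrected, and it can be: according to Trial status, recruitment was still open at submission, with 64 patients randomised.

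**What to change.** Before analysis, state one margin and use it in the sample size section, in H0 and H1, and in the Fig. 3 legend.

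If 5.3 and 166 patients are kept:

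1. Change M in the Fig. 3 legend and its hypotheses to 5.3.
2. Remove the sentence that accepts a 1.35-point loss, and remove 6.67 − 1.35 as the derivation.
3. Describe 5.3 as resting on clinical judgement and on the chronic fatigue syndrome derivation, and state that it exceeds the historical lower limit of 2.70.
4. Check the regulatory attribution against its source, and keep it only if the source supports it.
5. Prespecify that the confidence limit is also read against 2.70 and 1.35; that meeting 5.3 supports only a statement that blended CBT is not more than 5.3 points worse; and that retained benefit over nurse consultation is claimed only if a loss of 2.70 is excluded.

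**Cost.** Wording changes, two reference lines on the graph and no extra patients, but a weaker claim. With 75 per arm and no true difference, power is about 35–49% to exclude 2.70 and 16–20% to exclude 1.35 (SD 13.05 to 10.22); the protocol should disclose this. Adopting 1.35 as the margin would instead need 2,312 evaluable patients (SD 13.05) or 1,418 (SD 10.22), against the planned 150.
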